## **IX - STATISTICAL DATA MANAGEMENT**

### **IX.1 - RESPONSIBILITY FOR THE DATA ANALYSIS AND SOFTWARE USED**

The statistical analysis will be carried out independently by a blinded statistician from the Epidemiology, Biostatistics and Clinical Research Department of the Cochin Hôtel-Dieu Broca Hospital Group, using Statistical Analysis System version 9.1, under the responsibility of [name] and [name]. A statistical analysis plan will be prepared and validated prior to the freezing of the database and the unblinding.

The health economics evaluation will be carried out by [name].

## **IX.2 - JUSTIFICATION OF THE REQUIRED NUMBER OF SUBJECTS**

The first primary endpoint is the percentage of patients able to be discharged from the surgical department on D4, plus or minus 1 day. The expected percentage in the control arm is 20%. The sample size of 130 patients per arm will allow for an odds ratio of 2.15 (logrank test) with a power of 90% for a p-value of 2.5% in bilateral formulation in order to take into account the double endpoint. The second primary endpoint is the WOMAC function area under the curve analysis at 6 months. The total number of 260 subjects enrolled (130 per group) will allow to demonstrate an effect size of 0.45 for comparison of the average areas under the curve with a power equal to 90% (p-value equal to 2.5%, Mann-Whitney test). Taking into account approximately 10% losses-to-follow-up before the procedure, the number of patients to be enrolled into each study arm will be approximately 150, giving a total of 300.

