### **2. Primary endpoint analysis**

a) The percentage of patients able to be discharged from the surgical department on D4, plus or minus 1 day, will be compared between the 2 groups using the Chi-squared test. Furthermore, analyses adjusted for possible confounding factors (such as patient weight) will also be carried out using a logistic regression model. In addition, an operator effect will be added secondarily to the model to take into account the correlation between the time periods observed in patients operated on by the same surgeon in the event that there is an operator effect present. The results of the adjusted models will be compared to the non-adjusted model.

b) The WOMAC area under the curve between enrolment and 6 months will be calculated using the trapezoidal rule. The mean areas under the curve will be compared using the non-parametric Mann-Whitney test. In the event of missing data after the initial visit, an area under the curve of 1 will be used.

The endpoint tests will be considered significant at the 2.5% threshold so as to take into account the double primary endpoint.

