### **3.3 Calculation of the required number of subjects**

The calculation of the required number of subjects is detailed in protocol version no. 5.0 dated 07/04/2017.

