## **4 Principles of analysis**

### **4.1 General principles for the endpoint analysis**

The results will be reported in line with the CONSORT 2010 recommendations.

The endpoint analysis will be carried out in the ITT population.

The statistical analysis will be carried out with blinding in terms of the randomisation group.

No interim analysis is planned for this trial.

All the endpoints will be tested for superiority.

As the analyses are based on modelling or other numerical approaches, they require verification of the underlying hypotheses as well as convergence of their algorithms. If these conditions are not verified, an alternative method will be used.

The analyses will be carried out using R software version 3.4.4 or later (The R Foundation for Statistical Computing, Vienna, Austria).

The tests used will be bilateral with a significance threshold of 2.5% for the two primary endpoints and 5% for the secondary endpoints. The 2.5% threshold was chosen to take into account the double primary endpoint.

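### Protocol IX.2 states 90% power for the discharge-ability endpoint, but its own inputs give about 68% by the protocol's chi-squared test, and the log-rank test it cites is not planned

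*Supplement*

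**What the plan says.** Protocol section IX.2 gives every input of the calculation for the first primary endpoint. On the control rate: "The expected percentage in the control arm is 20" per cent. On the size, effect and power: "The sample size of 130 patients per arm will allow for an odds ratio of 2.15 (logrank test) with a power of 90" per cent. The threshold is a two-sided 2.5%, chosen because there are two primary endpoints. About 10% losses before surgery raise 130 to about 150 enrolled per arm.

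The endpoint is binary. Protocol VI.1 defines it as the percentage of patients independent on all four tests on the day of discharge. SAP 5.1.1 uses one assessment per patient: D5 if present, otherwise D4, otherwise D3.

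On the analysis, protocol IX.4 says the percentage "will be compared between the 2 groups using the Chi-squared test", with logistic regression in support. SAP 5.1.2 replaces this with a GEE Poisson model for the rate ratio, clustered by surgeon, with centre as a fixed effect, on multiply imputed data. SAP 4.1 keeps the threshold: "The tests used will be bilateral with a significance threshold of 2.5% for the two primary endpoints". The SAP has no calculation of its own; section 3.3 says "The calculation of the required number of subjects is detailed in protocol version no. 5.0 dated 07/04/2017".

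**The concern.** The power sentence joins parts that do not belong together: an expected percentage, an odds ratio and a log-rank test. A log-rank test needs event times and is powered through a hazard ratio and a number of events. Neither the protocol nor the SAP plans such an analysis for this endpoint. A 15-point difference on a 20% base with 130 per arm at 2.5% also looks too small for 90% power.

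At stake is how a null result on one of the two primary endpoints would be read. A reader who trusts 90% would take it as fair evidence against an effect of this size. The trial is to be reported under CONSORT, so the stated figure would carry into the publication.

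**Working it through.** **Inputs** (protocol IX.2): p0 = 0.20, odds ratio 2.15, n = 130 per arm, two-sided alpha 0.025 (z = 2.241), stated power 90%.

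**Step 1: experimental-arm rate.** Control odds are 0.20/0.80 = 0.25. Experimental odds are 0.25 × 2.15 = 0.5375, so p1 = 0.5375/1.5375 = 0.3496. The difference is 0.1496 and the mean rate is 0.2748.

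**Step 2: attempt to reproduce 90% with the protocol's chi-squared test.** Power = Φ[(difference × √n − z × √(2·p̄(1−p̄))) / √(p0(1−p0) + p1(1−p1))].
- Difference × √130 = 1.706
- 2.241 × 0.6313 = 1.415
- Denominator = 0.6224
- (1.706 − 1.415)/0.6224 = 0.467, so power = 68.0%

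The 90% is not reproduced. Other forms of the two-proportion test at the same n and alpha agree: exact enumeration of the chi-squared test 68.3%, unpooled variance 69.1%, arcsine 68.6%, Wald test on the log odds ratio 66.8%, Yates correction 63.3%.

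**Step 3: other evaluable numbers.** With 135 per arm (150 less 10%), power is 69.8%. With all 150 evaluable, it is 74.9%.

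**Step 4: what 90% would take.** n = [(2.241 × 0.6313 + 1.282 × 0.6224)/0.1496]² = 218.8, so 219 evaluable per arm. With 130 per arm, 90% is reached at 20% vs 39.8%, an odds ratio of about 2.65.

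**Step 5: the log-rank label taken literally.** Read 2.15 as a hazard ratio and 20% as the control event rate. The experimental event rate is 1 − 0.8^2.15 = 0.381. Expected events are 130 × (0.200 + 0.381) = 75.5. Schoenfeld's formula needs 4 × (2.241 + 1.282)² / (ln 2.15)² = 85 events for 90%. With 75.5 events, power is Φ(√75.5 × 0.765/2 − 2.241) = 86.1%; Freedman's form gives 82.4%.

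**Step 6: changing a stated input.**

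| Reading | Power |
|---|---|
| Chi-squared, 130 per arm, two-sided 5% | 77.4% |
| 2.15 as a risk ratio (20% vs 43%), 130 per arm, 2.5% | 96.5% |
| Log-rank, hazard ratio 2.15, 150 per arm, 2.5% (Schoenfeld) | 90.8% |
| Log-rank, hazard ratio 2.15, 130 per arm, two-sided 5% (Schoenfeld) | 91.4% |

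The last two come near 90%, but one uses the loss-inflated n and the other drops the alpha split that the sentence claims. Both use a test that is not planned.

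**Step 7: check of the method on the second endpoint.** Effect size 0.45, 130 per arm, two-sided 2.5%: Φ(0.45 × √65 − 2.241) = 91.7%. With an assumed Mann-Whitney efficiency of 0.955, it is 90.4%. The protocol's 90% for the WOMAC area under the curve therefore does reproduce, and the shortfall is specific to discharge ability.

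**The case against.** - **The sentence may be a remnant of a time-to-event plan.** Ability is assessed daily from D1 to D5, and the operator-effect sentence in protocol IX.4 still speaks of correlated time periods within a surgeon. With 2.15 as a hazard ratio and 150 per arm, power is about 90%. This is a plausible origin but remains inference. It does not make the sentence right for a percentage tested by chi-squared.
- **68% is not the power of the SAP's primary analysis.** This stands. A plain Wald test on the log rate ratio, without clustering, gives about 65% at 130 per arm and 72% at 150. The effects of surgeon clustering, centre adjustment and imputation cannot be computed from the documents. The 68% must therefore be labelled an unadjusted chi-squared approximation.
- **130 is the pessimistic number.** Partly fair: 150 per arm are to be enrolled. The result is best given as 68% at 130, rising to 75% if all 150 are evaluable.
- **The analysis itself is untouched.** True. No endpoint, dataset or estimate changes, and SAP 5.1.2 requires the difference and ratio with standard errors, which limits over-reading of a bare p-value.

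A reader might also infer that the fixed 2.5% per endpoint wastes power and should give way to a stepwise rule such as Holm's. The documents do not support calling it an error: protocol IX.2, protocol IX.4 and SAP 4.1 all state the split, it controls the family-wise error, and it gives simple 97.5% intervals that match each test. It is a valid design choice.

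**Conclusion.** The stated power is wrong as written. For 20% vs 35.0% at two-sided 2.5%, 130 per arm gives about 68% by the protocol's chi-squared test, or about 75% with 150 evaluable. The chance of missing the stated effect is about 32% at the planned 130, roughly three times the 10% implied. No reading tried at the stated n and alpha comes within 2 points of 90%, and the cited log-rank test belongs to no planned analysis of this endpoint.

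This rests on the protocol's own control rate, odds ratio, n and alpha, and on independent patients. Two things do not follow. The 68% is not an estimate of power for the GEE Poisson analysis. And the 219 per arm shows the size of the gap; it does not show that enrolment must rise, since the second primary endpoint is powered as claimed and 130 per arm still detects 20% vs 40% with 90% power.

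**What to change.** In protocol IX.2, delete the log-rank label and replace the power statement for the first endpoint with wording such as:

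> With 130 per arm, power is about 68% (75% with 150 evaluable per arm) for 20% vs 35% (OR 2.15), or 90% for 20% vs 40% (OR about 2.65), at two-sided 2.5%, by an unadjusted chi-squared approximation. Surgeon clustering, centre adjustment and imputation in the SAP analysis are not accounted for.

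Because SAP 3.3 only points to the protocol, it should refer to the corrected text. Leave the 2.5% thresholds and the statement for the second endpoint as they are. The change costs wording only, and the stated power becomes less favourable. Enrolment, endpoints and analyses stay the same.

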## **IX.3 - ANALYSIS STRATEGY FOR COLLECTED DATA**

An intention-to-treat analysis will be carried out. All randomised patients will be analysed and each patient will be analysed in the group to which they have been randomised, regardless of the technique received.

## **IX.4 - JUSTIFICATION OF STATISTICAL TESTS**

### **1. Descriptive statistics**

The descriptive statistics will be presented in the form of absolute and relative frequencies for the qualitative variables and means with standard deviation and range for the quantitative variables.

### **2. Primary endpoint analysis**

a) The percentage of patients able to be discharged from the surgical department on D4, plus or minus 1 day, will be compared between the 2 groups using the Chi-squared test. Furthermore, analyses adjusted for possible confounding factors (such as patient weight) will also be carried out using a logistic regression model. In addition, an operator effect will be added secondarily to the model to take into account the correlation between the time periods observed in patients operated on by the same surgeon in the event that there is an operator effect present. The results of the adjusted models will be compared to the non-adjusted model.

b) The WOMAC area under the curve between enrolment and 6 months will be calculated using the trapezoidal rule. The mean areas under the curve will be compared using the non-parametric Mann-Whitney test. In the event of missing data after the initial visit, an area under the curve of 1 will be used.

The endpoint tests will be considered significant at the 2.5% threshold so as to take into account the double primary endpoint.

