## **II - STUDY OBJECTIVE**

### **II.1 - PRIMARY OBJECTIVE**

The primary objective of this study is to assess the effectiveness of the programme on:

- ability, at discharge from the surgical department at D4, plus or minus 1 day, to carry out lying-sitting and sitting-standing transfers, walk 30 metres and go up and down one flight of stairs;
- speed of postoperative functional recovery within the first 6 months (area under the curve of the function subscale of the WOMAC index).

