### **III.2 - STUDY DURATION**

The planned enrolment period is 45 months. The study is therefore expected to last 60 months. The patients taking part in the study will be monitored for between 14 and 15 months depending on the time elapsed between the enrolment visit and the intervention for the multidisciplinary programme.

The patients will not be able to take part in a biomedical research study with therapeutic assessment likely to change the primary and secondary endpoints of the EDEX study for a duration of 15 months.

Following the study, there is no exclusion period during which participation in another study is prohibited.

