### **EXPERIMENTAL ARM:**

The sessions take place in groups (4 to 6 patients) and include education, performance and teaching of a personalised exercise programme. These sessions begin at least 2 months before the knee arthroplasty is performed.

**Supervised session schedule:** 2 supervised sessions lasting 1 and a half hours per week over 2 weeks.

**Content:** Programme preparation and planning are carried out according to the Medical Research Council Guidance recommendations for developing and evaluating complex interventions [Craig *et al.* 2008]. The intervention is developed and defined by a group of experts including orthopaedists, physical medicine and rehabilitation physicians, rheumatologists, physiotherapists, dieticians, psychologists and education science specialists. The group defines the main components of the intervention, its objectives, potential barriers, how to overcome them and how to optimise patient adherence to the messages received.

**Therapeutic education sessions (Annex 7):** in order to optimise the effect of the messages received, we tested the hypothesis already suggested in other situations (Munjanja SP 1996, Ravaud 2008) that an intervention proposing fewer, but more targeted, messages is more effective than a standardised education programme. To this end, 4 education classes are proposed with very different, simple messages.

In order to improve patient adherence, the first session is dedicated to physical activity before undergoing a TKA and walking after this surgery. The other 3 sessions are based on a single component (orientation at discharge, dietary advice and environment planning). This enables the message to be simplified, better understood by patients and easier to remember. In order to standardise the intervention, training sessions are organised for each of the educational sessions, and group support is provided.

It is made up of four 30-minute sessions before the exercise sessions:

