## **VII.1 - VISIT V0 - ENROLMENT VISIT**

The patients selected within the surgical department at Clermont-Ferrand University Hospital and Lariboisière and Cochin hospitals will be contacted by the clinical study technician and, if they are potentially interested in the study, they will be referred to the PMR departments at Cochin and Clermont-Ferrand and the Lariboisière rheumatology department for their enrolment visit and their study follow-up.

At the enrolment visit, the rehabilitation physician or the rheumatologist, with the help of the clinical study technician, will systematically confirm the inclusion and exclusion criteria. The study methods will be clearly explained to the patient. The patient will be given an information sheet and informed consent form. If the patient agrees to take part in the study, he or she will sign the informed consent form.

The following information will be collected in the electronic case report form:

- Demographic parameters (age, sex);
- Socioprofessional parameters (level of studies, profession and professional status (working, on sick leave, on disability, retired));
- Medical examination (weight, height and BMI);
- Inclusion and exclusion criteria;
- Information and consent;
- Demonstration of how to use the pedometer to measure the number of steps taken in the week after the enrolment visit;
- Co-interventions (particularly analgesics and/or NSAIDs, physiotherapy).

Patients will fill in a self-assessment card during the visit, including assessment of the following:

- knee pain over the past 48 hours, assessed using a visual numeric scale from 0 to 100;
- preference regarding hospital discharge destination and RAPT scale (Annex 6);
- function according to the WOMAC scale and the personalised section;
- quality of life (MOS SF-12, Annex 4 and EQ-5D-3L, Annex 5).

The time elapsed between the enrolment visit and the start of the multidisciplinary programme will be no more than one month.

**Randomisation:** patients will be randomised using CleanWeb software.

After randomisation, the patients in the two arms will receive a copy of the Knee Arthroplasty Guide (Annex 11).

The patients randomised into the “standard-treatment” control arm will receive standard medical care.

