### **VII.3 - FOLLOW-UP VISITS AFTER THE INTERVENTION**

#### **VII.3.1 - PREOPERATIVE VISIT (V1)**

At the preoperative visit, which will take place one or two days before the surgery, the following information will be collected in the electronic case report form:

- Professional status;
- Number of steps measured by the patient in the week (7 days) before this visit;
- Co-interventions since the enrolment visit;
- Adverse events.

Patients will fill in a self-assessment card including assessment of the following:

- knee pain over the past 48 hours (numeric scale);
- function according to the WOMAC scale and the personalised section;
- quality of life (MOS SF-12);
- adaptation of environment.

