## **5.2 Speed of functional recovery**

### **5.2.1 Definition**

The second primary endpoint is the speed of postoperative functional recovery at month 6. This is assessed using the area under the curve of the function subscale of the WOMAC index. The area under the curve will be defined by the trapezoidal rule.

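### The co-primary WOMAC area is computed from enrolment in the protocol, although the endpoint is postoperative recovery, and the SAP states no start point

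*Supplement*

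**What the plan says.** Protocol II.1 sets the second primary objective as "speed of postoperative functional recovery within the first 6 months (area under the curve of the function subscale of the WOMAC index". Protocol VI.1 places the assessment 6 months after surgery. SAP v2.0, section 5.2.1, agrees on the target: "The second primary endpoint is the speed of postoperative functional recovery at month 6".

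The calculation rule does not match. Protocol IX.4, primary endpoint analysis (b), states: "The WOMAC area under the curve between enrolment and 6 months will be calculated using the trapezoidal rule". SAP 5.2.1 says only: "The area under the curve will be defined by the trapezoidal rule". It names no start point, no time unit, no division by duration and no rule on actual or nominal dates. The model in SAP 5.2.2 contains arm, centre and a surgeon effect. It includes neither enrolment WOMAC nor waiting time.

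Four statements fix the timing before surgery:

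- Protocol VII.1: "The time elapsed between the enrolment visit and the start of the multidisciplinary programme will be no more than one month".
- Protocol V.1, experimental arm: "These sessions begin at least 2 months before the knee arthroplasty is performed".
- Protocol III.2: patients are "monitored for between 14 and 15 months depending on the time elapsed between the enrolment visit and the intervention for the multidisciplinary programme". The last contact is 12 months after surgery.
- Protocol VII.3.1, on the next WOMAC measurement: "At the preoperative visit, which will take place one or two days before the surgery".

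**The concern.** The only window written down anywhere is not the window of the endpoint it is meant to measure. A trapezoid from enrolment adds to each patient's area a block equal to the waiting time multiplied by the mean of the enrolment and preoperative scores. That block describes the unoperated knee. It adds variance to the area. It adds treatment effect only as far as the programme changes function before surgery.

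This is one of two co-primary endpoints, tested at 2.5%, and its sample size rests on an effect of 0.45 SD for the area. If 0.45 SD is meant for postoperative recovery, the same benefit is a smaller standardised effect on the longer area. If the analyst instead picks a start point when the SAP is applied, the definition of a primary endpoint has been left open.

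**Working it through.** **Planned sample size.** Protocol IX.2 gives an effect size of 0.45, 90% power, a 2.5% level (two-sided per SAP 4.1), a Mann-Whitney test and 130 per group. The two-sample normal formula gives 123 per group. Dividing by the Mann-Whitney efficiency 3/π = 0.955 gives 129, against 130 stated. Power at 130 per group is Φ(0.45 × √(130 × 0.955/2) − 2.241) = Φ(0.45 × 7.88 − 2.241) = 90.4%. The stated size is reproduced.

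**Length of the preoperative block.** Follow-up of 14 to 15 months less 12 months after surgery leaves 2 to 3 months. The enrolment-to-programme limit (0 to 1 month) plus the two-month minimum gives the same range. As a share of the window this is 2/(2+6) = 25% to 3/(3+6) = 33%.

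**Assumptions, none from the documents.** SD 18 at every visit; equal correlation between visits, 0.5 (range 0.3 to 0.7); WOMAC mean 50 at enrolment and V1, then 38, 30, 27, 25 and 23.

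**Area from V1 to month 6.** With visits at 0, 1.5, 3, 4, 5 and 6 months, the trapezoid weights are 0.75, 1.5, 1.25, 1, 1 and 0.5. They sum to 6 and their squares sum to 6.625.

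- SD = 18 × √(0.5 × 6.625 + 0.5 × 36) = 83.1 point-months.
- An effect of 0.45 SD is 37.4 point-months.

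**Area from enrolment, with the same 2.5-month wait for everyone.** Enrolment gets weight 1.25 and V1 rises to 2.0. The weights sum to 8.5 and their squares to 11.625.

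- SD = 18 × √(0.5 × 11.625 + 0.5 × 72.25) = 116.6.
- With no preoperative effect, d = 37.4/116.6 = 0.32 and power = Φ(0.321 × 7.88 − 2.241) = 61%.

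Nobody's wait varies in this calculation, so the loss comes from the block and not from the spread of waits. By simulation (Mann-Whitney, 130 per arm, 2,000 trials, correlations 0.3 to 0.7), uniform waits of 2 to 3 months in both arms give 58% to 61%, against 90% to 91% for the area from V1. Dividing the area by its duration leaves power at about 60%. At d = 0.32, about 255 per group would be needed for 90% power.

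**With a preoperative effect.** Hold the V1-to-month-6 effect at 37.4 and let the programme lower the V1 score. The enrolment-based area gains 1.25 × the V1 improvement.

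| V1 improvement | Effect on area | d | Power |
|---|---|---|---|
| none | 37.4 | 0.32 | 61% |
| 0.2 SD (3.6 points) | 37.4 + 4.5 = 41.9 | 0.36 | 72% |
| 0.45 SD (8.1 points) | 37.4 + 10.1 = 47.5 | 0.41 | 83% |

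Simulated values under similar assumptions run from about 70% to about 81%.

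**If the waits differed by arm (hypothetical).** A wait longer by 0.5 month in one arm adds about 0.5 × 50 = 25 point-months to an area not divided by duration. With no true effect and waits otherwise of 2 to 3 months, simulated rejection rates against a nominal 2.5% are:

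| Longer wait in experimental arm | Area not divided | Area divided by duration |
|---|---|---|
| 0.25 month | 7% to 12% | about 3% |
| 0.5 month | 22% to 36% | 4% to 5% |

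The shift counts against the arm that waits longer.

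**The case against.** The later SAP replaces the protocol's test and its missing-data rule, and it calls the endpoint postoperative. An analyst working from the SAP could therefore start at V1 or at surgery without contradicting it. That is correct: the SAP does not confirm the enrolment start. It does not withdraw it either, so the conflict stands.

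Counting function from randomisation is a defensible choice for a preoperative programme, and a real preoperative gain would recover part of the power. This also stands, and it is why the 60% figure holds only for no preoperative effect. An area of that kind would need a different name and objective.

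A reader might infer three stronger claims that the documents do not support:

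- **An unlimited wait.** No maximum is set between the sessions and surgery. But the follow-up statement and the one-month limit imply a planned 2 to 3 months, so power figures based on much wider waits fall outside the schedule.
- **Noise from variable waits as the cause of the dilution.** The fixed-wait calculation gives the same loss.
- **An actual bias between arms.** Only the experimental arm has the two-month rule, and surgeons are not blinded, so a difference could arise. But arthroplasty is already scheduled when patients become eligible, and nothing says that dates are moved by arm. The bias also needs an area that is not divided by duration. The protocol's substitute value of 1 for missing data could hint at a scaled area, though no scaling is defined and WOMAC runs from 0 to 100.

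**Conclusion.** The concern holds as a mismatch between the protocol's stated window and the endpoint it serves, which the SAP leaves unresolved. This part rests on the text alone and is certain.

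The cost of reading the window literally is conditional. With the assumed SD and correlations and no preoperative effect, about 30 points of power are lost. With a preoperative improvement of 0.2 to 0.45 SD the loss is roughly 10 to 20 points. The figures use the protocol's Mann-Whitney test; the SAP's mixed model was not simulated.

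Bias from unequal waits should be treated as a risk to monitor, not as a finding. The sample-size calculation itself is sound for an effect of 0.45 SD on whichever area is analysed.

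**What to change.** - **SAP 5.2.1:** define the area as running from the preoperative visit V1 (time 0) to month 6 after surgery, by the trapezoidal rule on actual assessment dates.
- **Protocol IX.4:** replace the enrolment start so that it matches.
- **SAP 5.2.2:** add enrolment WOMAC function as a covariate. V1 is measured after randomisation, so it belongs in the outcome and not among the covariates.
- **Sensitivity analysis:** keep the enrolment-to-month-6 area, divided by its duration.
- **Reporting:** give the time from enrolment to surgery by arm.

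The cost is a few sentences in the SAP and one in the protocol. WOMAC is already collected at enrolment, V1, 6 weeks and months 3 to 6. The downside is that any benefit during the waiting period then counts only through the V1 value. The sensitivity analysis keeps that benefit in view.
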